**Fig. 2 Fig2:**
[figure not shown]
Restricted randomization of the trial. This figure shows how we carried out restricted randomization for the study. We stratified *quartiers* depending on the child diarrheal prevalence, and within each stratum we grouped the *quartiers* into two (shown graded and ungraded in the figure) in order to ensure that *quartiers* in the same villages are allocated to the same arm and also to allocate the same number of *quartiers* to the treatment and control arms. *Quartiers* in the green boxes were selected as representative for each group in each stratum, and the leaders from the *quartiers* participated in the randomization activity, selecting an envelope containing a paper marked O or X without knowing which it would be before they opened it. For instance, if the leader of *Quartier* 1 selected an envelope with O, all the *quartiers* from Q1 through Q5 were to be allocated to the treatment group and Q6 through Q10 were remaining for the control group. Using this method, there were 8 different possible allocation scenarios for the trial. (Village and quartier name) V1: Bangabanga, V2: Bwalenge, V3: KalangandaMukeni, V4: Mayanda, V5: Ingundu, V6: ImpiniNnsi, V7: Punkulu, V8: IntswemLabwi, Q1: Bangabanga1, Q2: Bangabanga2, Q3: MbuluEbeth, Q4: Mbulesal, Q5: Ibansi, Q6: Center, Q7: Lakam, Q8: Ndjili, Q9: Nganda, Q10: Orondi, Q 11: Camp Center de Sante, Q12: Camp Musanga, Q13: Ekong, Q14: ImbilEngwow, Q15: Tshikapa, Q16: BwalaNgundu, Q17: Eban, Q18: Sante Labwi2

One of the greatest limitations of restricted randomization lies in the risk that it could bring about biased estimates of effect, especially when there is any difference across the clusters in the possibility of allocation to any given treatment [27]. However, we believe the possibility of a biased result was quite low in our study because there was no difference across *quartiers* in their probability of allocation to the treatment or control arm (Fig. 3).

**Fig. 3 Fig3:**
[figure not shown]
Flow diagram

### Primary health outcome

The primary outcome of the study is reduction in diarrheal incidence (cases per 1000 child-week), prevalence and average duration (days per episode) in children under four. To measure progress, the mother or caregiver of each household will record the diarrheal episodes of the youngest child under four on a daily basis using the ‘Sanitation Calendar’ (Fig. 4). The Sanitation Calendar will enable us to look into the intervention’s effects on incidence density as well as the duration of diarrhea in children under four. A 7-day recall period will be used to measure diarrheal prevalence.

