**Methods:**

This study describes the design of a cluster-randomized trial in Idiofa, the Democratic Republic of the Congo, seeking evidence of the impact of improved sanitation on diarrhea for children under four. Of the 276 quartiers, 18 quartiers were randomly allocated to the intervention or control arm. Seven hundred and-twenty households were sampled and the youngest under-four child in each household was registered for this study. The primary endpoint of the study is diarrheal incidence, prevalence and duration in children under five.

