### Sample size calculation

Based on the findings of the preliminary survey, we estimated diarrhea prevalence in Idiofa Territory to be 10%. We also made an assumption that the intervention would reduce the prevalence by 2.5% (25% relative reduction) on the basis of systematic reviews. Unlike the previous studies, we calculated sample size on the basis of *Incidence density of diarrhea by ‘child-weeks’* using formula [28] as follows:

The expected value of s^2^ is given by:

E(s^2^) = *λ* Av(1/y_j_) + *σ*
^2^
_c_ = *λ*Av(1/y_j_) + k^2^
*λ*
^2^,where λ is the true mean rate, y_j_ is the child-weeks of follow up in the j^th^ cluster, Av(1/y_j_) indicates the mean over all m clusters, σ^2^
_c_ is the between-cluster variance of true rates, and k is the coefficient of variation of those rates (22). Using the preliminary survey, we were able to determine that the overall diarrheal rate for the 20 *quartiers* was 0.1 (or 10 per 100 child-weeks). The empirical standard deviation of the observed diarrhea rates was s = 0.051216, and the average of the reciprocal child-weeks per *quartier* was Av(1/y_j_) =0.022222, so that k was estimated as follows:$$ {\widehat{\sigma}}^2=0.0{51216}^2\hbox{--} \mathrm{0.10.022222}=0.000401,\mathrm{therefore},\mathrm{k}=\surd \left(0.000401/0.1\right)=0.063 $$

With an assumption that the diarrhea rate in control *quartiers* remains constant at λ_0_ = 0.1, we required 80% power (z_β_ = 1.96) if the intervention is to reduce the diarrhea rate by 25% to λ_1_ = 0.10×0.75=.075. Assuming y = 540 child-weeks of observation in each *quartier*, the number of *quartiers* required in each treatment group is given by:$$ \mathrm{c}=1+{\left(1.96+0.84\right)}^2\left[\left(0.1+0.075\right)/540+{0.063313}^2\left({0.1}^2+{0.075}^2\right)\right]/{\left(0.1-0.075\right)}^2=6.14 $$

Ignoring clustering, y = (1.96 + 0.84)^2^(0.1 + 0.075)/(0.1–0.075)^2^ = 2195.2 child-weeks per group, corresponding to 2195.2/540 = 4.07 *quartiers*. Thus, the expected design effect for this trial would be 6.14/4.07 = 1.51.

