In addition, the Sanitation Calendar is to be used as an effective method of tracking diarrhea for a registered child. With the Sanitation Calendar, the incidence density of diarrhea can be calculated by dividing diarrhea cases by observed child numbers multiplied by the specific duration observed (e.g. week, month, etc.). This would be a more effective tool since it would cause less fatigue among the respondents, who would otherwise be asked to provide information about their children’s diarrheal episodes on a daily basis by interviewers. Assuming that the incidence of diarrhea among children is three times a year on average [32], the number of days marked ‘O’ in mothers’ diaries will not be very high. As for the duration of diarrhea, it was estimated at 10–20 days on average. Except for the days marked with ‘O,’ all the other days will be considered ‘X’. The Sanitation Calendar allows the day-to-day observation of diarrhea and resolves the limitations associated with the small number of clusters in the trial. Previous studies were unable to identify the effect of improved sanitation on diarrheal duration because they relied on the period prevalence of reported diarrhea. The utilization of the Calendar will enable us to explore a relationship between sanitation improvements and diarrhea and investigate the extent to which well-equipped and appropriately managed latrines affect disease duration. The measurement relying on caregivers’ reports, which are subjective in nature, is one of the limitations of this study. As we will not be able to conduct laboratory tests to assess children’s diarrhea incidence, there may be under-reporting or over-reporting of diarrhea. Despite this risk, we do not expect any significant difference of reporting patterns between the people of the intervention and control *quartiers*.

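### Three outcomes are jointly primary but only one is sized, and mean days per episode does not give a randomised comparison

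*Protocol article*

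**What the plan says.** - **Primary health outcome:** this section reads "The primary outcome of the study is reduction in diarrheal incidence (cases per 1000 child-week), prevalence and average duration (days per episode"; the age limit it gives is four years. Incidence and duration come from the daily Sanitation Calendar; prevalence comes from a 7-day recall.
- **Abstract, Methods:** "The primary endpoint of the study is diarrheal incidence, prevalence and duration in children under five". These are the same three outcomes with a different age limit.
- **Sample size calculation:** the authors write that "we calculated sample size on the basis of" a single quantity, "Incidence density of diarrhea by ‘child-weeks". They add "we required 80% power", use 1.96 + 0.84 in the formula, and assume "the intervention is to reduce the diarrhea rate by 25% to" 0.075. The same section opens with "we estimated diarrhea prevalence in Idiofa Territory to be 10" per cent, and later describes the intervention-arm figure as 7.5% prevalence. Rate and prevalence are used interchangeably for the same numbers.
- **Data analysis:** incidence density and 7-day prevalence are named as quantities to be calculated. Duration is not.
- **Discussion:** duration is presented as a distinctive contribution ("Previous studies were unable to identify the effect of improved sanitation on diarrheal duration"). Average episode length is put at 10 to 20 days, with no standard deviation and no target reduction. Any day not marked O is to be read as X.

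**The concern.** Two problems arise from one sentence.

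First, three different measures share primary status, while the calculation covers one of them and spends the whole 5% on it. A reader of the eventual results cannot tell from this document which outcome decides the trial, or what happens if they disagree.

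Second, mean days per episode is defined only where an episode occurs. If the intervention changes who falls ill, or which kinds of episode occur, the two arms contribute differently selected episodes. A difference in the mean then mixes selection with any real change in how long an illness lasts. Correcting for multiple testing would not cure this. A beneficial intervention could look neutral or harmful on a declared primary outcome, or appear to shorten illness without shortening any episode.

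**Working it through.** **Inputs.** From Sample size calculation: λ0 = 0.10 and λ1 = 0.075 per child-week, y = 540 child-weeks per quartier, k = 0.063313, z values 1.96 and 0.84, nine quartiers per arm, at least 12 weeks of follow-up. From Discussion: episode length 10 to 20 days on average. Correlations between tests and mixes of episode length are my assumptions.

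**1. The plan's own figures.**
- Without clustering: 2.8² × 0.175 / 0.025² = 2195.2 child-weeks, and 2195.2 / 540 = 4.07 quartiers. This reproduces.
- With clustering: 1 + 2.8² × [0.175/540 + 0.063313² × (0.1² + 0.075²)] / 0.025² = 5.85. The article prints 6.14, so this does not reproduce. That is a separate matter. What counts here is that the formula is for a rate in child-weeks at undivided z = 1.96, and that no second calculation exists.

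**2. Family-wise error, if any one of three 5% tests counted as success.**
- Independent, two-sided: 1 − 0.95³ = 14.3%.
- Independent, false favourable result only: 1 − 0.975³ = 7.3%.
- Equal pairwise correlation, two-sided, by simulation of a trivariate normal: 12.5% at 0.5, 9.8% at 0.8, 8.3% at 0.9.

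**3. What splitting alpha would cost.** Power for incidence with nine quartiers per arm is Φ(0.025 / √(V/8) − z), where V = 0.175/540 + k² × 0.015625.
- With the printed k = 0.0633: 95% at 0.05, and 89% at 0.05/3 = 0.0167.
- The article defines the between-cluster variance as k²λ², which gives k = √0.000401 / 0.1 = 0.20. Power is then 63% at 0.05 and 46% at 0.0167.

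One primary outcome avoids that loss.

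**4. Who enters the duration comparison.** Assume Poisson episodes at the design rates over 12 weeks. The share of children with at least one episode is 1 − exp(−12 × 0.10) = 70% in the control arm and 1 − exp(−12 × 0.075) = 59% in the intervention arm.

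**5. How the mean can move (hypothetical).** Let half of control episodes last 10 days and half 20, so the mean is 15. In each row below the intervention averts 25% of episodes and changes the length of none. Figures are per control-arm episode.

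| Averted | Diarrhoea days | Mean days per episode |
|---|---|---|
| Half of the short ones | 0.25×10 + 0.5×20 = 12.5 (−17%) | 12.5/0.75 = 16.7 (+11%) |
| A quarter of each | 0.375×10 + 0.375×20 = 11.25 (−25%) | 11.25/0.75 = 15.0 (0%) |
| Half of the long ones | 0.5×10 + 0.25×20 = 10.0 (−33%) | 10.0/0.75 = 13.3 (−11%) |

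Total days fall in every row. Mean duration rises, stays or falls according to which episodes were prevented.

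**The case against.** **No rule for success is stated.** A reader might infer that the trial has a 14.3% chance of a false claim. The document does not support that. The 1.96 is a sample-size input, not a testing rule, and hierarchy and alpha allocation are commonly left to an analysis plan, which is not shown here. The three outcomes are also measured in the same children and are probably correlated. This objection stands in full against the headline figure, and requiring all three outcomes to succeed would cost power instead. It does not remove the fact that the protocol itself names three primary outcomes and sizes one.

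**The calculation also speaks of prevalence.** True, but its denominator is child-weeks and it has no term for a 7-day recall measure. Table 1 gives baseline under-four prevalence of 45.9% and 45.7% (recall period not stated there), which makes it doubtful that 10% describes the recall measure. Nor should a reader infer that incidence is soundly powered because it is the one sized: the printed arithmetic does not reproduce.

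**Selective prevention of short episodes is invented.** A reader might infer that latrines will appear harmful on duration. Nothing in the document says which episodes would be averted, and the table shows that the mean could equally fall. The 7-day prevalence, taken over all children, would also help reveal a fall in burden. What remains is that the direction is unknown and randomisation does not protect the comparison.

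**Duration missing from Data analysis.** In a condensed article that alone proves little. It supports the point only because duration is declared primary.

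**Conclusion.** The concern holds in a limited form. Three outcomes are jointly primary, one calculation exists, and it concerns incidence density at undivided alpha.

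The error inflation is conditional: at most 14.3% two-sided under independence and an any-one-wins rule, 12.5% to 8.3% at assumed correlations of 0.5 to 0.9, and 7.3% for a false favourable result under independence.

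The firmer part is duration. Days per episode is conditional on illness after randomisation, with about 70% and 59% of children contributing under the design rates and a Poisson assumption. The size and direction of any distortion cannot be known from the document; the 11% shifts shown above are illustrations. The under-four and under-five wording is a minor inconsistency, but it touches the population of the primary endpoint.

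**What to change.** - Name calendar incidence density in the registered children as the single primary outcome. The Discussion already frames its conclusion on incidence.
- Make 7-day recall prevalence secondary.
- Assess the duration question as diarrhoea days per child-day of observation over all registered children. Report days per episode descriptively only.
- State that unmarked days are treated as missing, and reconcile this with the Discussion, which counts every day not marked O as X. The calendar instructions ask caregivers to mark X on diarrhoea-free days, so blanks can be told apart. Report calendar completeness by arm.
- Tie the comparison to the period before the control arm receives the intervention (Study design). The 12-week and 12-month observation periods given elsewhere need to be squared with that window.
- Use the same age wording in the Abstract and in Primary health outcome, and say how babies born during the study enter the registered group.

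**Cost.** No new data are needed, but this is more than rewording, because the rule for unmarked days changes. Prevalence and duration lose primary status. The last survey was planned for February 2017 and the article appeared in September 2017, so the change to published outcomes must be reported openly as an amendment, with its date relative to data access.

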**Fig. 4 Fig4:**
[figure not shown]
Sanitation Calendar (left: front, right: back)

### Eligibility criteria and enrollment

In selecting *quartiers*, we took into account the following eligibility criteria: (1) the lowest coverage of improved sanitation, (2) the lowest coverage of improved water, and (3) no other WASH projects scheduled to roll out from 2015 to 2016.

Households with at least one child under 4 years of age were eligible for this study. The youngest under-four child in each household was registered and assigned an identity number for the longitudinal study, as the follow-up period is about 1 year (Jan. 2016-Feb. 2017) and the cohort would be aging throughout the study. As we will follow an open cohort design, new babies born during the longitudinal survey period are to be enrolled for the study. Child age was verified with a Child Registration Card indicating the birth date of each child. We specifically targeted households with children under five because the majority of morbidity and mortality associated with diarrhea occurs in this group, and thus they are most likely to benefit from the intervention.

A total of 720 households were surveyed out of the 1399 households in the 18 *quartiers* chosen to be the subjects of the study. No household refused to be registered in the study. We obtained informed consent from 720 household heads in a written form. We established three teams, each consisting of six data collectors and one supervisor. A *quartier* was divided into three blocks, and a team was assigned to each block. Each team member started enrolling households from the central location of the block until s/he reached her/his quota or the assigned boundary of the block. In addition, a questionnaire survey was administered for the purpose of identifying WASH status, demographic characteristics and socioeconomic conditions. We achieved a remarkable balance of basic and WASH-related characteristics between the two arms (Table 1).

**Table 1 Tab1:** Balancing Results

Variable	Intervention	Control	Mean Difference	*P*-value
Diarrhoeal Prevalence (U4Y)	45.9%	45.7%		1.0
Diarrhoeal Prevalence (6–19)	12.4%	11.4%		0.731
Diarrhoeal Prevalence (20–39)	12.4%	14.3%		0.511
Diarrhoeal Prevalence (40~)	4.3%	4.3%		1.000
Latrine coverage (Unimproved)	60.3%	68.0%		0.036
Latrine coverage (Improved)	0%	0%		-
H/H Head gender (male)	88.6%	89.7%		0.719
H/H Head age	40.1(11.64)	40.85(10.92)	0.892	0.401
H/H/H Ethnic group	97.3%	99.4%		0.177
Education level (secondary)	62.4%	62.0%		0.351
Education level (primary)	30.5%	30.9%		0.945
H/H H religion (Christian)	92.4%	97.1%		0.004
Income	25,903 (50,536.12)	23,889 (36,762.34)	2014.44	0.574
H/H members	6.15(2.26)	6.09(2.28)	− 0.060	0.724
No. of U5C	1.66(0.77)	1.59(0.68)	− 0.079	0.146
Mother/Caretaker’s age	30.19(8.96)	31.08(8.96)	0.888	0.192
Youngest under-5 child age (months)	19.83(13.94)	19.95(14.12)	0.122	0.907
Latrine Utilization by all members	6.8%	4.6%		0.413
Main source of water (not-protected)	98.6%	94.6%		0.004
Average time for fetching water (minutes)	115.14(11.07)	94.29(10.51)	− 20.849	0.000
Water quantity (liter)	49.94(52.69)	65.06(51.97)	15.113	0.000
Duration of water storage (days)	2.75(1.56)	2.46(1.25)	− 0.286	0.008
Water container cleaning	96.6%	97.9%		0.478
Water treatment	3.5%	5.1%		0.359
HW Practice (Before eating)	94.5%	96.3%		0.150
HW Practice (After defecation)	86.6%	83.5%		0.719
HW Practice (Before cooking)	61.9%	62.6%		0.469
HW Practice (After cleaning child buttock)	6.7%	8.2%		0.301
HW Practice (After handling a sick person)	17.6%	14.3%		0.426
Latrine type (covering)	5.8%	2.9%		0.170
Latrine type (roof)	86.1%	81.9%		0.254
Latrine type (superstructure)	65.5%	70.6%		0.271
Latrine type (feces)	24.2%	16.8%		0.050
Latrine type (less than 50 cm)	24.7%	19.3%		0.178
Latrine type (flies)	69.5%	59.7%		0.032
Latrine type (flies quantity)	30.3%	19.7%		0.045

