The degree of latrine improvement will be scored according to the well-equipped latrine criteria. This will allow us to assess whether and how the diminishing effect of well-equipped latrines on diarrhea incidence among children under four differs depending on the degree of latrine improvement. Previous studies [14, 15] exploring the health benefits of sanitation have not paid attention to the possibility that the effect of latrines might vary depending on the degree of their improvement. Although a recent trial [21] reported an increase in access to one’s own latrine from 33 to 64.8% in rural Mali, they found no effect of a community-led sanitation improvement on the children’s diarrhea. Based on the 5-f theory, the Joint Monitoring Programme defines an “improved sanitation facility as one that hygienically separates human waste from human contact,” highlighting the importance of accounting for improvement status of latrines. In the case of pit latrines, the existence of a slab and hand-washing facilities, pit-hole depth and number of flies could be considered criteria for identifying the improved status of latrines. Applying these criteria, the proportion of improved latrines in Pickering et al. (i.e., latrines with concrete slabs) would be reduced to less than 30%. Focusing solely on the presence or access to any latrine type may mask the genuine health benefits of improved latrines.

The study hypothesis was not disclosed to people subject to the trial, though the general objectives were explained to them when obtaining informed consent. Thus, people are highly unlikely to be aware of the arm to which they belong because the sanitation intervention will continue to be executed in the control arm during the second phase. We thus surmise that the underreporting of diarrheal prevalence among the caregivers with a household latrine will not be a serious problem in this study. However, the limitation of not blinding still remains in this study since having a latrine is explicit in itself and many of the WASH committee members in the control arms were aware of the intervention even from the beginning due to their participation in the community lottery activity for random allocation.

Since the trial’s randomization process yielded remarkably balanced results between the two arms, and since no other intervention is expected to roll out until February 2017, any differences observed in diarrheal incidence can be attributable to latrine improvement.

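### The protocol claims balanced arms and uses that to credit latrines with any difference, but its own Table 1 shows clear baseline differences, mainly in water access.

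*Protocol article*

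**What the plan says.** In the protocol article, Eligibility criteria and enrollment, the baseline comparison is summarized as "We achieved a remarkable balance of basic and WASH-related characteristics between the two arms", with Table 1 as the evidence.

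The last part of the Discussion makes this a premise: "Since the trial’s randomization process yielded remarkably balanced results between the two arms". Together with the expectation that no other intervention will arrive before February 2017, it leads to the conclusion that "any differences observed in diarrheal incidence can be attributable to latrine improvement".

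The Study design section describes the allocation. Eighteen quartiers were stratified into three groups by child diarrhea prevalence. Each stratum was split into two groups that kept quartiers of one village together, and an envelope draw decided the arm. The article gives eight possible allocations.

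The Data analysis section names generalized estimating equations, a log-binomial model, a random-effects model and a multi-level analysis. It names neither a baseline covariate nor the strata.

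**The concern.** The balance statement explicitly covers WASH-related characteristics, and those are where Table 1 shows the arms apart. The rows that differ are not incidental. The Background names flies, contaminated fields and water as routes of transmission, and feces and flies as features of latrine management to be studied.

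The statement also does inferential work, because the Discussion uses it to rule out explanations other than latrines. If it is wrong, a difference in diarrhea, or the absence of one, may partly reflect how the arms started. The design makes this likely: three draws between pairs of village-based groups give chance little opportunity to even out water supply, which tends to be shared within a village.

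**Working it through.** **Inputs.** Means, standard deviations, percentages and p-values come from Table 1. The text states 360 households per arm. The Table 1 percentages fit 370 and 350 better (170/370 = 45.9%, 160/350 = 45.7%), so those sizes are used below as an assumption. Average cluster size is 720/18 = 40. The article gives no intracluster correlation (ICC) for these variables, so 0.01 to 0.10 is assumed.

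**1. Size of the differences (intervention vs control)**

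| Variable | Intervention | Control | Difference |
|---|---|---|---|
| Fetching time, min | 115.14 | 94.29 | 20.85/94.29 = 22% longer |
| Water quantity, L | 49.94 | 65.06 | 15.12/65.06 = 23% less |
| Unprotected source | 98.6% | 94.6% | 4.0 points |
| Water storage, days | 2.75 | 2.46 | 0.29 days longer |
| Unimproved latrine coverage | 60.3% | 68.0% | 7.7 points lower |
| Under-four diarrhea | 45.9% | 45.7% | 0.2 points |

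In standard-deviation units the gap is 1.93 for fetching time, 0.29 for water quantity, 0.22 for unprotected source, 0.21 for storage and 0.16 for latrine coverage.

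**2. Reproducing the table's p-values.** Fisher's exact test on 223/370 vs 238/350 gives 0.036 for latrine coverage, as printed. Unprotected source (365/370 vs 331/350) gives 0.002 to 0.0045 depending on the test, against 0.004. A two-sample t-test gives 0.006 for storage, against 0.008, and below 0.001 for fetching time and water quantity, both printed as 0.000. The printed values are therefore household-level tests that take no account of quartiers.

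**3. Allowing for clustering.** Divide the household-level statistic by √[1 + (40 − 1) × ICC] and refer it to t with 16 df.

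- Water quantity: SE = √(52.69²/370 + 51.97²/350) = 3.90, and 15.12/3.90 = 3.88. At ICC 0.05 the design effect is 2.95, so t = 3.88/1.72 = 2.26, p = 0.04. At ICC 0.10 it is 4.9, so t = 1.75, p = 0.10.
- Fetching time: SE = √(11.07²/370 + 10.51²/350) = 0.804, and 20.85/0.804 = 25.9. At ICC 0.10, t = 25.9/2.21 = 11.7, p < 0.001.
- Unprotected source: p = 0.02, 0.04, 0.10 and 0.20 at ICC 0.01, 0.02, 0.05 and 0.10.
- Storage: p = 0.03, 0.06, 0.13 and 0.23 at the same values.
- Latrine coverage: p = 0.09, 0.13, 0.23 and 0.35.

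**4. Feces and flies.** The printed p-values fit only restricted denominators. Among latrine owners (223 and 238), feces 54 vs 40 gives Fisher 0.0503 (printed 0.050), and flies 155 vs 142 gives 0.0322 (printed 0.032). Fly quantity among latrines with flies, 47/155 vs 28/142, gives 0.0447 (printed 0.045). With all households as denominator the same percentages would give about 0.017, 0.006 and 0.001, which do not match. Spread over all households, the counts become:

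- feces: 54/370 = 14.6% vs 40/350 = 11.4% (3.2 points, p = 0.22)
- flies: 155/370 = 41.9% vs 142/350 = 40.6% (1.3 points, p = 0.76)
- fly quantity: 47/370 = 12.7% vs 28/350 = 8.0% (4.7 points, p = 0.05)

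**5. The allocation.** Three strata with one draw each give 2³ = 8 allocations, so any single allocation has probability 1/8 = 0.125. The 16 df in step 3 treat the quartiers as separately randomized and are generous.

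**The case against.** **Counting significant rows.** Table 1 has 35 rows with a p-value, and nine are at or below 0.05 against 35 × 0.05 = 1.75 expected. A reader might infer that randomization failed. That does not follow: the tests ignore clustering, the rows are correlated (four concern water supply and storage, four concern latrine coverage and condition), and one of the nine is exactly 0.050.

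**A uniformly disadvantaged intervention arm.** A reader might also infer this, and hence a bias against the intervention. The document does not support it. The Background says poorly equipped latrines can themselves spread disease, so more unimproved latrines in control is not clearly an advantage. Other rows lean towards the intervention arm: use by all members 6.8 vs 4.6%, pit cover 5.8 vs 2.9%, roof 86.1 vs 81.9%, hand-washing after defecation 86.6 vs 83.5%. The fly and feces gaps shrink per household. All 18 quartiers were chosen for a water supply program, so the baseline water differences may not persist.

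**Outcome balance.** Baseline diarrhea in the target age group is nearly identical. This is reassuring, but expected after stratifying on it, and it does not make the WASH characteristics balanced.

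**No covariates named.** It is tempting to say the analysis will be unadjusted. The article does not say so, and a covariate list may stand in an analysis plan that is not shown.

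All four objections limit the point. None restores the balance statement or the attribution drawn from it; both are in this article, and no analysis plan would cure them.

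**Conclusion.** The concern holds in a limited form: the article asserts balance on WASH-related characteristics that its own table contradicts, mainly for water. The firm evidence is fetching time and water quantity. Fetching time stands out at every ICC considered; water quantity does so up to an assumed ICC of 0.05 but not at 0.10. Unprotected source, storage and latrine coverage differ in size but are compatible with chance once moderate clustering is allowed for.

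These differences are what a design with eight allocations can be expected to produce, and they are no evidence of faulty randomization. The consequence is for interpretation: balance cannot be the reason for ascribing any difference to latrines. The direction and amount of any confounding cannot be determined from the document.

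The result rests on arm sizes of 370 and 350 and the latrine-owner denominators, both inferred from the printed figures, on assumed ICCs, and on reading the bracketed fetching-time figures as standard deviations. If they were standard errors, the statistic would be 20.85/√(11.07² + 10.51²) = 1.37, which does not agree with the printed p of 0.000.

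**What to change.** 1. Withdraw the balance statement under Eligibility criteria and enrollment. Describe the differences by size, noting that the p-values ignore clustering, and state the denominator of each latrine row.
2. Remove the Discussion sentence that attributes any difference to latrines because the arms are balanced. Rest the causal claim on randomization together with the adjusted analyses.
3. Include randomization stratum and baseline diarrhea prevalence in the primary model, unless the analysis plan already does so.
4. Prespecify one adjusted sensitivity analysis with a short list (water quantity, fetching time, water source), using a method suited to 18 clusters, such as a two-stage analysis of cluster residuals.

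The cost is small. The variables were collected at baseline, so the change is in wording and a little analysis work. At cluster level, three strata use 2 df and baseline prevalence 1 df, leaving 16 − 3 = 13. The covariate list must stay short for that reason.
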